## Methods

This study is a non-blinded randomised crossover controlled trial. Following the completion of a screening visit to confirm study eligibility (Pre-Screening; visit 1), each participant will complete a single load carriage exercise session on two separate occasions (visits 2 and 3) completed in a randomised order; one with a calcium supplement (Supplement) (1000 mg) and one without (Control) (Fig. 1). Block randomisation using a block size of 2 will be performed and there will be no allocation concealment. All laboratory testing will be completed at the Army Human Performance Laboratory based at the Royal Military Academy, Sandhurst, UK.

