#### Maximal rate of oxygen uptake

An incremental maximal exercise treadmill test (ELG, Woodway, USA) will be performed to determine $$\dot V$$O_2max_ [34]. Participants will run on the treadmill at a starting speed of 5 km·h^−1^ with the speed increased by 1 km·h^−1^ per minute until volitional exhaustion. Expired gases (Metalyzer 3B, Cortex, Germany) and heart rate (H10, Polar, Finland) will be measured continuously. Maximal rate of oxygen uptake will be taken as the highest 30 s average $$\dot V$$O_2_. Where $$\dot V$$O_2max_ criteria is not attained (34) $$\dot V$$O_2peak_ will be reported.

### Load carriage 1 and 2

Participants who meet the inclusion criteria from pre-screening will complete two independent load carriage exercise sessions in the laboratory separated by a minimum of two weeks. Participants not taking any hormonal contraceptives will track their menstrual cycle with the provided menstrual diary and start each experimental testing session in the late lutal phase/early follicular phase (within the few days just before or after menstruation). Participants using the combined oral contraceptive pill will complete each experimental testing session during the seven day break between pill packets; participants taking back-to-back combined oral contraceptive pill packets, using an intrauterine system, or intrauterine device will be tested at any point.

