In the 24 h preceding each load carriage session participants will be rested (no exhaustive exercise) and will not apply skin moisturizer. Participants will arrive at the laboratory after an overnight fast, have an indwelling cannula inserted in a vein in the antecubital fossa, and a resting blood sample taken (Fig. 2). A calcium supplement (2 × 500 mg; Calcichew) will be given to each participant completing the Supplement condition ~ 60 min before starting the load carriage exercise [8]. Sweat collectors (Macroduct Sweat Collector, ELITech Group, France) [35] will be attached to the forearm for the measurement of sweat calcium excretion during exericse. A 120 min session of load carriage exercise will be completed. The load carriage exercise is a fitness test completed by the infantry. Participants will walk 12.8 km on the treadmill at 6.4 km·h^− 1^ for 120 min whilst wearing a 20 kg military backpack. Expired gases, heart rate, and rating of perceived exertion will be measured throughout the exercise. The first urine void upon waking (Fig. 2), and a urine void within ~ 1 h of the cessation of load carriage, will be obtained for the measurement of calcium isotopes for the calculation of bone calcium balance. Nude body mass will be measured before and immediately after exercise for the determination of sweat loss and calculation of sweat calcium excretion; post-exercise body mass will be adjusted for water consumed *ad libitum* during exercise. Calcium concentration of water consumed during exercise will be recorded. Blood samples will be taken at 0 min, and then every 20 min during, and 15, 30, 60, and 90 min following, load carriage. Blood samples fractioned into serum and plasma will be analysed for markers of bone formation, bone resorption, and calcium metabolism. Whole blood will be analysed immediately for blood lactate concentration (Lactate Pro 2, Arkray, Japan), ionized calcium, haemoglobin and haematocrit (i-STAT Alinity, Abbott, USA; CHEM8^+^, Abbott, USA) (Fig. 2). Isokinetic (60°·s^− 1^ and 180°·s^− 1^) and isometric (90° knee flexion) maximal voluntary contraction of the knee extensors and flexors (System 4, Biodex Medical Systems, USA) will be measured before and immediately after load carriage exercise. Researchers will monitor the laboratory testing procedures to ensure adhereance to study protocols; there is no criteria for the study to be discontinued.

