**Fig. 2 Fig2:**
[figure not shown]
Overview of load carriage exercise testing protocol. ^a^Procollagen type 1 N-terminal propeptide, bone-specific alkaline phosphatase, beta carboxy-terminal cross-linking telopeptide of type 1 collagen, albumin-adjusted calcium, ionized calcium, ^44^Ca:^42^Ca, phosphate, intact parathyroid hormone, 25-hydroxyvitamin D, 1,25-dihydroxyvitamin D, 24,25-dihydroxyvitamin D, luteinising hormone, follicle stimulating hormone, oestradiol, testosterone, and sex hormone binding globulin will be measured before load carriage. ^b^Procollagen type 1 N-terminal propeptide, beta carboxy-terminal cross-linking telopeptide of type 1 collagen, ionized calcium, albumin-adjusted calcium, phosphate, intact parathyroid hormone, sclerostin and osteocalcin will be measured at 0 and 120 min during load carriage, then 30 and 90 min after load carriage. ^44^Ca:^42^Ca will be measured at 120 min during load carriage. ^c^Procollagen type 1 N-terminal propeptide, beta carboxy-terminal cross-linking telopeptide of type 1 collagen, ionized calcium, albumin-adjusted calcium, phosphate, and intact parathyroid hormone will be measured at 20, 40, 60, 80 and 100 min during load carriage, and 15 and 60 min after load carriage.

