#### Secondary outcomes

Circulating measures of calcium and bone metabolism during load carriage will be compared between Control and Supplement conditions, and changes in knee flexor and extensor strength will be compared between pre- and post-load carriage, using linear mixed models with the restricted maximum likelihood estimation to allow incorporation of incomplete data. Time and group (Control or Supplement) will be assigned as fixed effects and participant will be assigned as random effects to account for within participant correlation for repeated measures. Within exercise data will be compared between trials using paired sample *t*-tests.

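### As written, the secondary mixed model omits session-to-session variation within a woman, so the Supplement versus Control main effect for repeatedly sampled blood markers gets too small a standard error

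*Protocol article*

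**What the plan says.** All references are to the Protocol article.

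- **Outcomes and comparison** (Secondary outcomes): "Circulating measures of calcium and bone metabolism during load carriage will be compared between Control and Supplement conditions", using linear mixed models fitted by REML.
- **Fixed effects** (Secondary outcomes): "Time and group (Control or Supplement) will be assigned as fixed effects". No time-by-group interaction, period effect or baseline covariate is listed.
- **Random effects** (Secondary outcomes): "participant will be assigned as random effects to account for within participant correlation for repeated measures". No session or participant-by-condition term and no within-session covariance is named.
- **Design** (Methods): "each participant will complete a single load carriage exercise session on two separate occasions", one with and one without the supplement. Under Load carriage 1 and 2, the sessions are "separated by a minimum of two weeks".
- **Sampling** (Load carriage 1 and 2): "Blood samples will be taken at 0 min, and then every 20 min during, and 15, 30, 60, and 90 min following, load carriage".
- **Markers by time point** (Fig. 2 legend): one set "will be measured at 0 and 120 min during load carriage, then 30 and 90 min after load carriage", and a shorter list "will be measured at 20, 40, 60, 80 and 100 min during load carriage, and 15 and 60 min after load carriage". Together these give 11 time points for six markers (P1NP, βCTX, ionized calcium, albumin-adjusted calcium, phosphate, iPTH) and 4 for sclerostin and osteocalcin.

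**The concern.** Condition is applied to a session, not to a blood sample. For Supplement versus Control, the experimental unit is therefore the session within a woman, and there are two per woman. A participant random effect absorbs only what her two sessions have in common. Whatever shifts all samples on one day and not on the other stays in the residual. The model then treats that residual as independent from sample to sample and divides it by the number of samples.

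The protocol gives reasons to expect such day-to-day shifts. Sessions are at least two weeks apart. Users of an intrauterine system or device, or of back-to-back pill packets, are tested at any time. Water during exercise is unrestricted. A resting sample is taken before the supplement, but the stated model does not adjust for it.

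The outcomes are secondary, but they include PTH, ionized calcium and bone resorption, which the main hypothesis in the Background names. PTH also supports the second sample size calculation.

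**Working it through.** **1. The plan's own figures.** The PTH calculation (d = 0.667, α = 0.05, power 0.90, 26 people) reproduces as a two-sided paired t-test: power is 0.892 with n = 25 and 0.9045 with n = 26. The statement for 30 women (d = 0.75, α = 0.01) also reproduces as a paired test, with power 0.902. Both calculations use one difference per woman. The sample size therefore treats the between-session difference as the unit, and the stated mixed model does not.

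**2. Inputs.** From the documents: n = 30 women, two sessions each, m = 11 or m = 4 samples per session, significance at p < 0.05 (taken as two-sided). Assumed: session variance τ², because no document gives it. With σ² the sample-level variance, write r = τ²/σ². The session share of within-woman variance is s = r/(1 + r), varied from 0.1 to 0.5.

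**3. Formula.** For a value made up of participant + session + residual in balanced data:

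- True variance of the condition difference: 2(τ² + σ²/m)/n.
- Variance the participant-only model reports: 2·MSE/(nm), where MSE is about σ² + τ²·m/(2m − 1).
- Ratio of true to reported variance: R = (1 + m·r) / (1 + r·m/(2m − 1)).
- Actual type I error: 2·[1 − Φ(1.96/√R)].

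Example with m = 11 and s = 0.2, so r = 0.25: R = 3.75/1.131 = 3.32, √R = 1.82, 1.96/1.82 = 1.08, and the error rate is 28%.

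**4. Results.**

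| Session share s | r | R, 11 samples | Type I error, 11 samples | R, 4 samples | Type I error, 4 samples |
|---|---|---|---|---|---|
| 0.1 | 0.111 | 2.10 | 17.6% | 1.36 | 9.3% |
| 0.2 | 0.25 | 3.32 | 28.2% | 1.75 | 13.8% |
| 0.3 | 0.429 | 4.67 | 36.4% | 2.18 | 18.4% |
| 0.5 | 1 | 7.88 | 48.5% | 3.18 | 27.2% |

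Simulation of the balanced test (30 women, 10,000 trials per row) agrees with each rate to within one percentage point. At r = 0.25 and 11 samples, 200 REML fits of the stated model rejected in 25.5%, which fits 28% given the Monte Carlo error of about 3 points. With no session variance and independent samples, the rate is the nominal 5%.

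**5. Serial correlation alone.** With no session shift but AR(1) correlation between successive samples, the participant-only model rejects in about 25% of null trials at a correlation of 0.5, and in about 46% at 0.8 (11 samples).

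**6. With the session as the unit.** In balanced data, a session term is equivalent to a paired test on the session means (29 degrees of freedom). Its simulated error rate stays at about 4% to 5% in every setting above.

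**The case against.** **The article is condensed.** It says random effects in the plural and does not say intercept only. A participant-level condition slope would serve as the missing session term, and such detail may sit in a fuller document. This stands as a doubt about intent: the text does not exclude a session term. But participant is the only factor named, and it is said to handle the repeated-measures correlation. The sentence as written gives a participant-only model.

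**The hypothesis concerns a change over time.** Attenuating a fall in calcium or a rise in PTH is naturally a time-by-group question. Under an additive session shift, a participant-only model makes the interaction test conservative, not liberal: simulated type I error with 11 samples is 3.8%, 2.7%, 1.5% and 0.3% at shares of 0.1, 0.2, 0.3 and 0.5. This limits the point to the group main effect. It does not remove it, because the protocol lists no interaction, and the error term would be wrong for that test too.

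**Paired t-tests are also planned.** The last sentence of Secondary outcomes assigns these to within-exercise data. A paired test on one value per woman and session does not have this fault. The scope of that sentence is unclear, though, and the circulating markers are expressly given to the mixed model.

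**The size is assumed.** This stands. Some day-to-day variation is controlled by the overnight fast, 24 h without exhaustive exercise, cycle scheduling for some women, and inter-assay CVs of at most 3% on the main platform. With 4 samples and a 10% share, the inflation is only about two-fold.

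**Conclusion.** The point holds for the model as written. The Supplement versus Control main effect for the eight repeatedly sampled markers is tested with a standard error that leaves out between-session variation. For session shares of 0.1 to 0.5, the actual type I error at a nominal 5% is about 18% to 49% with 11 samples and about 10% to 27% with 4. These rates rest on an assumed session variance, an additive session shift, balanced data and a two-sided test. The inflation is absent only if a woman's sessions do not differ and her samples within a session are otherwise uncorrelated, which is hard to expect for samples 20 min apart.

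A reader might infer that a several-fold rise in false positives is established, or that every secondary result is compromised. The documents support neither. They give no session variance, and a time-by-group test would err in the other direction under an additive shift. The pre/post strength comparison is made within a session and is not affected in this way. The primary outcome is a single urinary change per session with its own analysis, so this point does not reach it.

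**What to change.** - **Model.** Add a random participant-by-condition (session) effect to the mixed model for circulating markers, with period as a fixed effect and Kenward–Roger degrees of freedom. A serial within-session covariance may be added to the session effect, but AR(1) should not replace it. With a participant intercept and AR(1) only, REML fits to the same scenario (400 per setting) still rejected in 16.5%, 23.5%, 26% and 34% of null trials at shares of 0.1, 0.2, 0.3 and 0.5.
- **Alternative.** Reduce each session to one summary, for example a baseline-adjusted AUC, and compare it in a paired model. This matches the unit used in the PTH sample size.
- **Contrast.** State whether the group main effect or the time-by-group interaction answers the hypothesis, and which data the paired t-tests cover.

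The change is to analysis wording only and uses samples already planned. The cost is wider confidence intervals for the condition effect, which is the correct width for two sessions per woman.

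### The paired t-test sentence does not say which exercise data it covers; read literally it overlaps the blood markers given to the mixed model, and neither method has a period term

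*Protocol article*

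**What the plan says.** The Secondary outcomes section of the protocol article names two methods for comparing the two conditions.

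- **Mixed model.** "Circulating measures of calcium and bone metabolism during load carriage will be compared between Control and Supplement conditions", and the method is fixed as "using linear mixed models with the restricted maximum likelihood estimation to allow incorporation of incomplete data". Its terms are listed: "Time and group (Control or Supplement) will be assigned as fixed effects and participant will be assigned as random effects". No period term, condition × time term or session-level random effect is named.
- **Paired t-test.** The last sentence reads "Within exercise data will be compared between trials using paired sample" *t*-tests. It names no variables, and does not say whether each time point or one summary per session is tested.

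The blood schedule is in the section on load carriage 1 and 2: "Blood samples will be taken at 0 min, and then every 20 min during, and 15, 30, 60, and 90 min following, load carriage". The Fig. 2 legend lists six analytes (P1NP, βCTX, ionized calcium, albumin-adjusted calcium, phosphate and intact PTH) that "will be measured at 20, 40, 60, 80 and 100 min during load carriage". It lists the same six, with two others, at 0 and 120 min, and describes both of those times as during load carriage. The load carriage section also has expired gases, heart rate and perceived exertion recorded throughout the march. No other analysis method is named for these three.

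**The concern.** Both sentences compare Control with Supplement on data gathered during the march, and nothing separates their scope. If the second includes the blood markers, three things follow.

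- A woman with one of her two samples missing at a time point drops out of that test, although the mixed model was chosen to keep such data.
- The same marker has two p-values, and the plan does not say which one decides.
- Nothing stops a separate test at every sampling time.

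PTH, ionized calcium and bone resorption are named in the study hypothesis, and PTH is the basis of the second sample size calculation. It therefore matters which test is used for them, even though they are secondary. The trial is also unblinded and the investigators assess the outcomes, so the choice of test is better closed in advance.

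Separately, this is a two-period crossover. A period effect (familiarity with the march or a training effect, for example) is removed only if the analysis contains a term for it.

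**Working it through.** **1. The plan's own figures.** Statistical analyses gives 26 women for PTH (d = 0.667, α 0.05, power 0.90), and 30 women for d = 0.75 at α 0.01. A two-sided paired t-test with the noncentral t distribution (degrees of freedom n − 1, noncentrality d√n) gives:

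- d = 0.667, α = 0.05: n = 26, power 0.905.
- d = 0.75, α = 0.01: n = 30, power 0.902.
- A two-sample test at d = 0.667 would need 49 per group.

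The stated numbers reproduce, and they rest on a paired t-test for PTH during exercise. This makes the literal reading of the t-test sentence credible. It does not prove it, because sizing a repeated-measures study by a paired test is a common simplification.

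**2. Number of tests if the markers are covered and each time is tested.** There are six markers (Fig. 2 legend). Times are 20 to 120 min (six), or seven with 0 min.

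- 6 × 6 = 36 tests; 36 × 0.05 = 1.8 false positives expected under the null.
- 6 × 7 = 42 tests; 42 × 0.05 = 2.1.

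These expectations hold whatever the correlation. The chance of at least one false positive does depend on correlation. For one marker at six times it is 1 − 0.95^6 = 0.265 if the times are independent. Simulation (20,000 runs, n = 30) with assumed correlation between times gives:

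| Correlation | Equal between all times | Decaying with distance |
|---|---|---|
| 0.5 | 0.21 | 0.23 |
| 0.8 | 0.14 | 0.17 |
| 0.9 | 0.11 | 0.13 |

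**3. Incomplete pairs.** If each sample is missing independently with probability m (assumed), the expected number of complete pairs at a time point is 30(1 − m)². Power is for d = 0.667 at α = 0.05, with pairs rounded.

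| m | Pairs | Power |
|---|---|---|
| 0 | 30 | 0.942 |
| 0.05 | 27.1 | 0.915 |
| 0.10 | 24.3 | 0.879 |
| 0.15 | 21.7 | 0.847 |

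The comparison is with 30 complete pairs. A mixed model would also lose information to missing samples, but it keeps the woman's other samples.

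**4. Period.** Let r be the period effect divided by the SD of the within-woman difference. With equal sequences, the Supplement minus Control difference is shifted by +r SD in one sequence and −r SD in the other. Ignoring period adds r² to its variance, so the SE is multiplied by √(1 + r²):

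- r = 0.25: √1.0625 = 1.031 (3%).
- r = 0.5: √1.25 = 1.118 (12%).
- r = 0.75: √1.5625 = 1.25 (25%).

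At r = 0.5, power for d = 0.667 with 30 women falls from 0.942 to about 0.88. With 15 and 15 women per sequence there is no bias. If per-protocol losses left 15 and 12 (assumed), (15 − 12)/27 = 0.11 of the period effect would enter the treatment estimate.

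The factor is derived for the paired comparison. The mixed model as written also has no period term, so a period effect goes into its error as well.

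**The case against.** The best defence is that the paragraph can be read without contradiction: named markers go to the named model, and the t-test sentence, which uses a different term, covers expired gases, heart rate and perceived exertion, for which nothing else is specified. That reading is reasonable. A reader might infer that the protocol definitely assigns the markers to both methods; the text allows this but does not establish it.

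On that narrower reading, a paired t-test on one mean per session would respect the pairing and give one test per variable. Nothing in the text says every time point is tested. This also stands, so a charge that the sentence necessarily ignores repeated measures would go too far. What remains is that no summary is named and period is left out.

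A reader might also multiply out 1 − 0.95^42 = 0.884 and quote an 88% chance of a false positive. That needs the contested reading, a test at every time and independent results. Serial samples from the same woman are not independent, so 88% is not a fair headline.

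Period omission is not special to the t-test, since the mixed model shares it. Randomising in blocks of 2 keeps the sequences close to balanced, so the main cost is precision unless losses unbalance them.

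Finally, a condensed article may leave detail to the full protocol or analysis plan. That would excuse silence. Here the article states two methods with overlapping wording, so the sentence itself needs correcting.

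**Conclusion.** The point holds in a limited form. The scope of the t-test sentence is undefined, and its plain meaning overlaps the markers already given to the mixed model.

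If the markers are included, complete-pair deletion works against the plan's stated reason for the model ("to allow incorporation of incomplete data"), two p-values compete, and 36 to 42 tests would yield about 2 false positives under the null. Per marker, the familywise error is about 0.11 to 0.23 instead of 0.05. If they are not included, what remains is an unnamed summary measure.

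On both readings, neither analysis adjusts for period, at a cost in precision that depends on a period effect the documents do not give.

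Assumptions: two-sided tests, correlations of 0.5 to 0.9 between times, independent missingness of 5% to 15%, and period effects of 0.25 to 0.75 SD. The primary ANCOVA is untouched by this point.

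**What to change.** - Exclude the circulating markers from the t-test sentence and analyse them only with the REML mixed model.
- In that model use condition, time, condition × time and period as fixed effects, with participant and session within participant as random effects. The session effect is needed because samples from the same march share variation that a participant effect alone does not capture.
- Base inference on one condition test, or one condition × time test, per marker. Label contrasts at single time points as descriptive or adjust them for multiplicity. Moving the contrasts into the model does not by itself limit their number, so this must be written down. With six markers, one test each gives 6 × 0.05 = 0.3 false positives expected under the null, in place of 1.8 to 2.1.
- Name expired gases, heart rate and perceived exertion explicitly. Analyse them with the same model, or as one session mean per woman in a within-woman comparison adjusted for period.

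The cost is a few lines of analysis text and a little extra modelling. No new data or visits are needed.
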